---

### **PROTOCOL SYNOPSIS**

**Title:** The effects of different degrees of semi-recumbent position during anesthesia emergence on postoperative hypoxemia in patients undergoing laparoscopic upper abdominal surgery

**Study Type:** A prospective, single-center, Randomized Controlled, Clinical Trial

**Corresponding Author:** [name], Department of Anesthesiology, Affiliated Hospital of Xuzhou Medical University, Xuzhou, Jiangsu, China. [name], Department of Anesthesiology, Xuzhou Central Hospital, Xuzhou, Jiangsu, China.

**Study Center:** Affiliated Hospital of Xuzhou Medical University

**Ethics:** Approved by the Ethics Committee of the Affiliated Hospital of Xuzhou Medical University (XYFY2021- KL090-01).

**Trial Registration:** [www.chictr.org.cn](http://www.chictr.org.cn) (ChiCTR2100045087)

30

31

---

## 59 I. STUDY OBJECTIVES

60 Annually 313 million surgical procedures are performed worldwide. However, few  
61 studies have explored the anesthesia emergence position in patients with general  
62 anesthesia. We aimed to investigate the efficacy and safety of different degrees of  
63 semi-recumbent position for anesthesia emergence.

64

65

66

67

68

69

70

71

72

73

74

75

76

77

78

79

## 80 **II. BACKGROUND**

### 81 **A. Postoperative hypoxemia**

82 Previous studies reported that hypoxemia, one of the most meaningful factors  
83 associated with poor patient outcomes, occurs in 10% to 50 % of patients after  
84 surgery, depending on the surgical population, definition of hypoxemia, and  
85 monitoring methods. Severe hypoxemia can result in arrhythmias, abnormal blood  
86 pressure changes, and nervous system damage, all of which adversely affect patients'  
87 postoperative recovery.

### 88 **B. Prevention and treatment of postoperative hypoxemia**

89 Although oxygen therapy can prevent and treat hypoxemia, many patients will still  
90 develop hypoxia in the PACU even with prophylactic oxygen. There have also been  
91 many studies regarding ventilatory techniques to improve postoperative lung function,  
92 but the benefits of protective ventilation techniques may be lost during emergence

---

process. Whalen et al. found that recruitment manoeuvre and the application of positive end-expiratory pressure (PEEP) improved intraoperative oxygenation, but the effect dissipated promptly during emergence process. Neither oxygen therapy nor protective ventilation techniques can completely eliminate postoperative hypoxemia, which means there is still room for improvement.

### C. Preliminary Studies

Currently, only a few studies have focused on the position during anesthesia emergence. Although there is no evidence to support a universal patient position for extubation, most anesthesiologists prefer to place patients in supine position. This is because it is simple, and enables easy observation. However, the reduction in functional residual capacity (FRC) caused by the supine position tends to promote airway closure and reduce gas exchange. Although, there is a growing preference for anesthesia emergence in semi-recumbent position. However, there is still a lack of reliable clinical evidence to demonstrate its efficacy, safety, and appropriate tilt angle. Therefore, we hypothesized that putting patients undergoing laparoscopic upper abdominal surgery in a semi-recumbent position during anesthesia emergence can reduce the incidence of postoperative hypoxemia.

---

### 137 **III. METHODS**

138 This is a prospective randomized, controlled trial that has been registered in the  
139 Chinese Clinical Trial Registry (ChiCTR2100045087) and has been approved by the  
140 Ethics Committee of the Affiliated Hospital of Xuzhou Medical University  
141 (XYFY2021- KL090-01). This report adheres to the CONSORT guidelines. The study  
142 was conducted according to the guidelines of the Declaration of Helsinki with Good  
143 Clinical Practice. All participants provided written informed consent before  
144 enrolment.

#### 145 **A. Recruiting Methods**

146 Potential participants to the study were identified from the elective surgery list.  
147 Patients aged  $\geq 18$  years, ASA I to III, and undergoing elective laparoscopic upper  
148 abdominal surgery under general anesthesia were eligible to participate. The study  
149 will involve the use of protected health information. The study site will gain

---

permission from each subject to use their protected health information by written authorization. All subjects will be identified by the anesthesiologist.

#### **B. Inclusion Criteria**

Patients aged  $\geq 18$  years, ASA I to III, and undergoing elective laparoscopic upper abdominal surgery under general anesthesia were eligible to participate.

#### **C. Exclusion Criteria**

Body mass index (BMI)  $> 35 \text{ kg} \cdot \text{m}^{-2}$ , emergency surgery, underlying lung disease, previous lung surgery, pneumothorax, pulmonary tuberculosis, pleural effusion, expectation of difficult intubation, respiratory failure, severe heart block (II or III atrioventricular block, double-bundle branch block), severe sinoatrial node dysfunction, congestive heart failure, pregnancy, and patient's refusal.

#### **D. Consent Procedure**

All potential subjects that are identified by the chief anesthetist and/or designee that meet the inclusion/exclusion criteria will be given the opportunity to participate. Guardians/patients will be given the consent/assent during the screening visit. They will be given the opportunity to review the consent/assent and ask questions about the study. Guardians/patients will be asked to summarize in their own words what participation in this research study involves and that they are comfortable with the risks and benefits of participating in the research study. Any additional questions they have will also be answered by the investigator prior to signing the consent/assent. Once the consent/assent form is signed, a signed and dated copy of the authorization form will be provided to the subject and another copy placed in the participant's medical record.

#### **E. Randomization and Blinding**

Randomization was performed using a computer-generated random numbers table with a block size of 6 and a 1:1:1 ratio after stratification according to the type of surgery and age. Allocation was sequentially numbered and sealed in opaque

---

envelopes by the corresponding author. The anesthesiologists opened the envelopes 10 min before the emergence procedure. Because of the nature of the intervention, full blinding of all study personnel was not feasible. However, to minimize bias, we attempted to blind patients, practitioners (where possible), research assistants, and data analysts. It was not feasible to blind the PACU anesthesiologists and nurses. To achieve patient blinding, during the informed consent process, we described all interventions as anesthesia emergence positions, and we explained that depending on group allocation, patients may receive different emergence positions during anesthesia emergence. We additionally performed an analysis of blinding success of patients using Bang's Blinding Index.

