#### **F. Sample Size Calculation**

The sample size for the primary outcome of this study was calculated with continuity correction, and was based on a ratio of exposed (combined 15-degree and 30-degree SRP) to unexposed (supine positioning) groups of 2:1. According to our pilot study, the frequency of hypoxaemia was 46% in the unexposed group, with a 26% relative (12% absolute) reduction in the exposed group. Assuming a two-tailed type I error rate of 5%, a sample size of 620 was needed to give greater than 80% power to detect a decrease in the incidence of hypoxaemia from 46% in the supine positioning group to 34% in the combined 15-degree and 30-degree SRP groups. Finally, we planned to recruit 700 patients to compensate for dropouts. The sample size calculation was conducted using the PASS 11.0 software (NCSS LLC).

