#### **G. Statistical Analysis**

Continuous variables were presented as mean (SD) or median (interquartile range, [IQR]), depending on whether the data was distributed normally or not. Categorical variables were presented as a number (percentage). The normal distribution of data was evaluated using the Shapiro–Wilk test, and the Levene method was used to test the homogeneity of variance. Differences in repeated measures variables were analysed by repeated-measures analysis of variance. Continuous outcomes were

analysed with one-way analysis of variance (ANOVA) or Kruskal-Wallis test. Categorical variables were tested using  $\chi^2$  test or Fisher's exact test. The primary analyses were performed according to the intention-to-treat (ITT) principle. Modified ITT (mITT) and per-protocol (PP) analyses were also performed as sensitivity analyses for the primary outcome. Results of primary and secondary outcomes were reported as relative risk (RR) or between-group difference with 95 % CI, the absolute risk reduction (ARR) and Number needed to Treat (NNT) were also calculated, with 95% CI. Kaplan-Meier curves were used for the time to first experience hypoxaemia. When an overall intervention effect was detected ( $P < 0.05$ ), the Bonferroni correction for multiple pairwise comparisons would be performed. To handle missing data, multiple imputations by chained equations was used, assuming missing data are missing at random. Imputation for continuous data was performed by predictive mean matching, logistic regression for binary variables. The number of imputations was 5. Convergence of the multiple imputation algorithm and the results of the imputation were checked. Imputations were performed with the R MICE package (J Stat Software. 2011;45(3):1–67.). Analyses were then performed on each of the imputed data sets and pooled according to Rubin's rules. As a post hoc sensitivity analysis, we used a logistic regression model simultaneously entering: age, BMI, current smoking status, chronic pain needing opioids, ARISCAT score (Assess Respiratory Risk in Surgical Patients in Catalonia), CCI (Charlson Comorbidity Index), surgery time, intraoperative opioid consumption, and the use of a nasogastric tube. R version 4.1.1 was used for statistical analysis, and analysis items with 2-sided  $P < 0.05$  were considered statistically significant.

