## **J. Measurements and Endpoints**

The primary outcome was the incidence of postoperative hypoxaemia in the PACU (defined as  $\text{SpO}_2 < 90\%$  for more than 10 seconds or  $\text{PaO}_2:\text{FiO}_2$  ratio below 300 mmHg). We also recorded the incidence of severe hypoxaemia ( $\text{SpO}_2 < 85\%$  for more than 10 seconds) and the time to first episode of hypoxaemia. Patients were continuously monitored real-time vital signs in the PACU using a Mindray BeneVision N15 monitor (Shenzhen Mindray Bio-Medical Electronics Co., Ltd.). In this study, data collection was performed by one-on-one researchers in the PACU, review of the monitor's database by the data collector when the patient leaving the PACU. To avoid pulse oximeter probe dislodging the finger or having it only partially on the finger, we used disposable finger probes that stick to the finger like a Band-Aid for continuous monitoring (Disposable  $\text{SpO}_2$  Sensor, Shenzhen Mindray Bio-Medical Electronics Co., Ltd.).

The secondary outcomes included:

airway rescue (defined as the need for mask noninvasive positive pressure ventilation, or re-intubation);

respiratory symptoms (coughing);

extubation time (defined as the time from end of surgery to extubation);

respiratory comfort (before leaving PACU, graded using a numerical rating scale, ranging from 0 to 10, higher score means more comfort);

duration of stay in the PACU;

wound pain (VAS score measured at rest, while coughing at 5 and 30 minutes after extubation, before leaving PACU, and 24 hours post operation);

and position-related adverse events (hypotension, arrhythmia, and some other adverse events).

The patient's vital signs (heart rate and mean arterial pressure) were recorded at six time points: (1) the beginning of surgery (T0); (2) the end of surgery (T1); (3) immediately after adjusting position (T2); (4) immediately prior to extubation (T3); (5) 1 min after extubation (T4); (6) when leaving the PACU (T5).

Dynamic lung compliance ( $\text{C}_{\text{dyn}}$ ) and driving pressure ( $\Delta P$ ) were also recorded at

---

320 three time points: (1) when stitching; (2) 5 minutes after adjusting position; and (3)  
321 before extubation.

322 Arterial blood gas analysis was performed at three time points: (1) when stitching; (2)  
323 5 minutes after adjusting position; (3) 5 minutes post-extubation.

324

---

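### Randomisation is stratified by type of surgery and age, but no stated analysis carries both factors; if they predict hypoxaemia, the unstratified primary test is somewhat conservative and forgoes some power.

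*Protocol*

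**What the plan says.** **Randomisation.** Protocol section III.E specifies blocks of 6 and a "1:1:1 ratio after stratification according to the type of surgery and age". It gives neither the surgery categories nor the age cut-points.

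**Outcome.** Section III.J: "The primary outcome was the incidence of postoperative hypoxaemia in the PACU". This is a yes/no outcome.

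**Test.** Section III.G: "Categorical variables were tested using" a chi-square or Fisher's exact test. No stratum term, stratified test or adjusted primary model is named. If the overall comparison of the three groups gives P < 0.05, Bonferroni-corrected pairwise comparisons follow.

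**Adjusted analysis.** Section III.G names one: "As a post hoc sensitivity analysis, we used a logistic regression model simultaneously entering: age, BMI, current smoking status, chronic pain needing opioids". The list continues with ARISCAT score and Charlson index and ends with "surgery time, intraoperative opioid consumption, and the use of a nasogastric tube". Age is in the model; type of surgery is not.

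**The concern.** Blocking within strata keeps the arms balanced on the stratification factors. That removes the between-stratum part of the outcome variation from the real sampling error of the treatment difference. An unstratified test, and unadjusted intervals for the relative risk and risk difference, still count that variation as noise. If the strata are prognostic, the standard error is then larger than the design warrants: the test rejects less often than 5% under the null, the intervals are too wide, and some power is given away.

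The sensitivity model does not close the gap, because it carries only one of the two factors. An analysis plan that the protocol leaves open would be no finding; here the protocol names both the test and the covariates.

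**Working it through.** **Step 1. Reproduce the planned sample size.** Inputs from section III.F: risks 46% and 34%, ratio 2:1 (k = 2), two-sided 5%, 80% power, continuity correction.

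- Mean risk = (0.46 + 2 × 0.34)/3 = 0.38.
- Uncorrected supine-arm size: n = [1.960 × √(1.5 × 0.38 × 0.62) + 0.842 × √(0.46 × 0.54 + 0.34 × 0.66/2)]² / 0.12² = 193.8, so 194 (582 in total).
- Corrected: (n/4) × [1 + √(1 + 2(k+1)/(k × n × 0.12))]² = (193.8/4) × [1 + √1.129]² = 206.1, so 207 (621 in total).

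The plan states 620, so the figure reproduces. At 620 the power for supine versus combined is 0.801 with continuity correction and 0.824 without. The calculation takes no credit for stratification.

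**Step 2. Expected direction and size.** Let R² be the share of outcome variance that lies between strata: variance of the stratum risks / (0.46 × 0.54). Under the null, with balanced strata, the unstratified statistic is too small by a factor of about 1 − R². Hence

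- three-group test (2 df, critical value 5.991): true alpha ≈ exp[−(5.991/2)/(1 − R²)];
- supine versus combined: true alpha ≈ 2 × [1 − Φ(1.96/√(1 − R²))].

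R² = 0.022 gives 4.7% and 4.7%. R² = 0.120 gives 3.3% and 3.7%. R² = 0 gives 5% for both.

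**Step 3. Simulation.** The protocol gives no stratum risks, so these are assumptions: four equal strata, N = 620, permuted blocks of 6 at 1:1:1 within strata, overall risks 46% versus 34%, 40,000 trials per setting. The unstratified chi-square without continuity correction is compared with the Cochran-Mantel-Haenszel (CMH) test over strata. Monte Carlo standard errors are about 0.1 point for alpha, √(0.05 × 0.95/40,000), and about 0.2 point for power, √(0.75 × 0.25/40,000).

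| Supine risk across strata | R² | Alpha, 3-group, unstratified | Alpha, 3-group, CMH | Power, 3-group, unstratified → CMH | Power, supine vs combined, unstratified → CMH |
|---|---|---|---|---|---|
| 46% in all | 0.000 | 0.051 | 0.051 | 0.736 → 0.736 | 0.823 → 0.823 |
| 36-56% | 0.022 | 0.045 | 0.048 | 0.744 → 0.751 | 0.830 → 0.835 |
| 30-63% | 0.063 | 0.040 | 0.049 | 0.747 → 0.770 | 0.836 → 0.850 |
| 23-69% | 0.120 | 0.034 | 0.051 | 0.740 → 0.788 | 0.837 → 0.866 |
| 15-78% | 0.230 | 0.021 | 0.050 | 0.754 → 0.844 | 0.857 → 0.908 |

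The simulated alphas agree with the formulas in step 2. Over 36-56% to 23-69%, the power forgone is 0.7 to 4.8 points for the three-group test (0.7506 − 0.7435; 0.7875 − 0.7396) and 0.4 to 2.9 points for supine versus combined (0.8347 − 0.8304; 0.8657 − 0.8372). Six strata, or N = 700, give similar results. With continuity correction, the unstratified supine-versus-combined test at N = 620 has power 0.80 to 0.83 across the table.

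**The case against.** **The effect is conditional.** A reader might infer that the true error rate is below 5% and that power is lost. The protocol does not support that as a fact. It gives no stratum risks, and the first row of the table shows no loss when the strata are not prognostic. The widest range is hard to defend in a population limited to elective laparoscopic upper abdominal surgery with lung disease, BMI above 35, respiratory failure and heart failure excluded (section III.C). This objection stands, and the conclusion is worded accordingly.

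**The planned power is intact.** A reader might also infer that the trial falls short of its target because of this omission. It does not: supine versus combined, the contrast used for sizing, keeps about 80% or more in every row. The three-group test has only about 0.74 at N = 620, but that comes from sizing on the combined contrast and is present even in the first row; it is a separate matter. What is forgone here is extra precision that the plan never counted on.

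**Sparse strata.** With unknown surgery categories crossed with age, some cells may be small or unequal, which the simulation did not cover. This stands, and is why a regression alternative is offered.

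**Two tempting extensions fail.** First, since the logistic model is written into the protocol, one might want to remove its post hoc label. Section III.G reports that analysis in the past tense and itself calls it post hoc; removing the label could present an unplanned analysis as prespecified. Second, one might want to adjust for PaO2:FiO2 at stitching, because that ratio is part of the outcome. It is not a stratification factor, the gain has not been quantified, and the protocol does not fix whether the sample precedes the opening of the envelope 10 minutes before emergence.

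**What remains.** No stated analysis carries both factors used to randomise. Age appears in one sensitivity model, so the gap there concerns type of surgery only.

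**Conclusion.** The point holds as an efficiency improvement. The primary test does not follow the randomisation, and the only adjusted model omits one of the two stratification factors. If the factors are moderately to strongly prognostic (supine risks of 36-56% to 23-69% across four equal strata, an assumption), the nominal 5% three-group test runs at about 4.5% to 3.4%, and the power forgone is about 0.7 to 5 points for that test and about 0.4 to 3 points for supine versus combined. If the factors are not prognostic, a stratified analysis costs essentially nothing. The error is on the conservative side: there is no inflation of the type I error, and validity is not in question.

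**What to change.** - Make the primary analysis stratified by type of surgery and age, using the randomisation categories: a CMH test with stratified relative risk and risk difference. If strata are sparse, use a modified Poisson model with group, type of surgery and age.
- State the surgery categories and age cut-points.
- Keep the unadjusted chi-square test as a sensitivity analysis.
- Add type of surgery to the listed logistic model, and keep its post hoc label unless it was in fact prespecified.

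**Cost.** No extra patients or data: both factors had to be recorded in order to randomise. Before outcomes are seen by group, this is a change of wording. Because parts of the protocol are written in the past tense, any change made after that point should be reported as such, with the stratified result given beside the test already stated.

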## H. Intervention

At the end of operation, patients were transferred from operating table to transfer bed, and their positions were adjusted according to the groups.

supine position group (group S): Patients were placed in supine position from the end of surgery to leaving PACU.

15-degree semi-recumbent position group (group F): Patients were placed in 15-

---

degree semi-recumbent position from the end of surgery to leaving PACU.

30-degree semi-recumbent position group (group T): Patients were placed in 30-degree semi-recumbent position from the end of surgery to leaving PACU.

The inclination angle was set precisely by an inclinometer (GeeLii 55157, Shanghai GeeLii International Trade Co., China)

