Prior to extubation, all patients underwent suctioning, with no further stimulation being applied until spontaneous movement was observed. Neuromuscular blockade was reversed using intravenous neostigmine 40 to 60 µg/kg combined with atropine 0.5 mg. Prior to extubation the following criteria had to be met: complete reversal of neuromuscular blockade (a Train-Of-Four ratio greater than 0.90); patient fully awake; and breathing adequately.

After extubation, conventional oxygen therapy (low-flow oxygen ( $\leq 15$  l/min) delivered either by Nasal cannula,  $\text{FiO}_2$  0.35, oxygen flow 3.5 l/min; or Venturi mask,  $\text{FiO}_2$  0.35, oxygen flow 9 l/min) was administered. The recovery nurses did not intervene in the patient's breathing before the onset of hypoxemia, and only when hypoxemia occurred did the recovery nurses correct the hypoxia by encouraging the patient to take deep breaths and increasing the  $\text{FiO}_2$ . In patients who developed  $\text{SpO}_2 < 90\%$  more than 1 minutes, rescue mask ventilation was applied. A decision to re-intubate was made by the anaesthetist in the PACU if the ROX index (defined as the ratio of pulse oximetry/fraction of inspired oxygen to respiratory rate) was less than 4.88. If there was evidence of hemodynamic instability, the intervention was cancelled by the anaesthetist.

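### Envelopes are opened before the patient is positioned, leaving a short, avoidable interval of known allocation that chiefly exposes extubation time

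*Protocol*

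**What the plan says.** Protocol section III.E describes sequentially numbered, sealed, opaque envelopes and fixes when they are opened: "The anesthesiologists opened the envelopes 10 min before the emergence procedure". The start of the emergence procedure is not tied to the end of surgery, the end of an infusion, transfer or reversal.

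The same section says of blinding that "full blinding of all study personnel was not feasible", which it attributes to the kind of intervention. It adds that "we attempted to blind patients, practitioners (where possible), research assistants, and data analysts", and that "It was not feasible to blind the PACU anesthesiologists and nurses".

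Section III.H places the start of the intervention later: "At the end of operation, patients were transferred from operating table to transfer bed, and their positions were adjusted according to the groups".

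Section III.J lists extubation time as a secondary outcome, "defined as the time from end of surgery to extubation". It also schedules the first blood gas and the first compliance and driving pressure readings during stitching, before the position is adjusted.

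**The concern.** A tilted bed makes it unavoidable that staff around the patient know the arm once the angle is set. It does not make it necessary for them to know beforehand. If the envelope is opened some minutes before positioning, anaesthetic care in those minutes can be given with the arm known, although the arms do not yet differ in treatment. The protocol's own aim was to blind practitioners where it could, and here it could.

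What is at stake is performance bias. Someone who favours head-up emergence might, without intending it, lighten anaesthesia sooner in the tilted arms. Extubation time would then differ between arms for a reason other than position, and the difference would be reported as an effect of position. The readings taken during stitching are the only pre-position values of compliance, driving pressure and blood gas, so arm-aware ventilator changes before them could also shift the reference for later readings.

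**Working it through.** No figure in the plan is in dispute. The check sets the timings and the rules of care side by side.

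**1. Length of the interval.** Measure time in minutes from the end of surgery. Let E be the start of the emergence procedure and P the moment the angle is set. The envelope is opened at E − 10, so the arm is known before positioning for

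L = P − (E − 10) = 10 + P − E, or zero if this is negative.

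Section III.H puts P at the end of the operation, after transfer. The transfer time is not given, so I take it as brief (P ≈ 0). Then:

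| Assumed start of emergence | E | L |
|---|---|---|
| End of surgery | 0 | 10 min |
| 5 min after end of surgery | 5 | 5 min |
| 10 min after end of surgery | 10 | 0 min |

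The first row is the natural reading. The title describes the intervention as the position during emergence, and section III.H runs that position from the end of surgery to leaving the PACU, so emergence appears to begin at about the end of surgery. The lower rows remain possible because the term is undefined.

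**2. What can be varied in that interval.** Under Perioperative management (III.I.ii), remifentanil (0.1 to 0.3 µg/kg/min) and propofol (4 to 12 mg/kg/h) are ranges with no stated stop time. PEEP is a lower bound, tidal volume an upper bound, and the recruitment manoeuvre has no stated time. Nothing freezes settings when the envelope is opened or gives this interval to someone unaware of the arm.

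**3. What is held in common.** The same section fixes a BIS of 40 to 60, inspired oxygen of 60% during surgery, rocuronium stopped about 40 minutes before the end of surgery, and shared extubation criteria, including a train-of-four ratio above 0.90. The BIS target does not say when infusions end. The extubation criteria fix the state to be reached, not how soon it is reached.

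**4. Route to extubation time.** Extubation time = time of extubation − time of end of surgery. If arm-aware care brings readiness for extubation forward by d minutes and leaves the end of surgery unchanged, the outcome falls by about d minutes. The document gives no value for d.

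**5. Route to the stitching readings.** On the first row of the table the envelope is opened about 10 minutes before surgery ends. No rule says whether stitching readings come before or after that, so their blindness is not assured.

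**6. Route to the primary outcome.** Hypoxaemia is assessed in the PACU, and a PaO2:FiO2 ratio below 300 mmHg counts towards it, with a blood gas 5 minutes after extubation. The route exists, but its size cannot be derived. The following is an illustration under assumptions, not an estimate: no true effect, a supine rate of 46%, 620 patients split 2:1 (n1 = 206.7, n2 = 413.3), an uncorrected two-sided 5% test, and a bias of b that lowers the rate in the tilted arms. The chance of a significant result favouring them is

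Φ{[b − 1.96·√(p̄(1 − p̄)(1/n1 + 1/n2))] / √(p1(1 − p1)/n1 + p2(1 − p2)/n2)}.

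For b = 0.02: p1 = 0.46, p2 = 0.44, p̄ = 0.4467. The numerator is 0.02 − 1.96 × 0.04235 = −0.0630, the denominator is 0.0424, and Φ(−1.486) = 6.9%. For b of 1, 3 and 5 points the chances are about 4%, 11% and 22%, against a nominal 2.5%. This shows what a bias of that size would do if it existed. It does not show that one exists.

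**The case against.** Several points on the other side stand.

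- **The window is inferred.** Because the start of emergence is undefined, the envelope might be opened at or close to transfer, with little or no interval before positioning. A reader might infer 10 minutes of arm-aware care in every patient; the text does not establish that.
- **The opener's role is inferred.** Section III.E speaks of anesthesiologists in general. A reader might take this to be the person giving the anaesthetic; the protocol neither says so nor excludes it.
- **Oxygenation is a weak route.** A reader might infer that the primary outcome is compromised. The common rules in step 3 limit the scope, the outcome is assessed later in the PACU, and staff there are openly unblinded.
- **Reversal is not a good example.** The neuromuscular block is "reversed using intravenous neostigmine 40 to 60 µg/kg", a range, but this is described among the steps before extubation and so probably follows positioning, when the arm is visible anyway.
- **The readings taken during stitching** are instrument or laboratory values, and the protocol does not call them baselines.
- **The procedure is largely protective.** Opaque envelopes opened late keep care arm-blind for most of the operation, and incomplete blinding is disclosed.

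These points limit the concern without removing it. The disclosure concerns unblinding that the intervention makes unavoidable, and this interval is avoidable. Opening at transfer would protect concealment at least as well. Nor can the post hoc logistic model be relied on as a repair: it enters intraoperative opioid consumption, which arm-aware remifentanil use could itself change, and it does not enter propofol.

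**Conclusion.** The concern holds in a limited form. On the natural reading, allocation is known to whoever opens the envelope for up to about 10 minutes before the position is set, and nothing in the intervention requires this. It is neither a contradiction nor a numerical error.

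The chief exposure is extubation time, a secondary outcome. The lesser one is the assurance that the stitching readings are arm-blind. An effect on postoperative hypoxaemia is possible but weaker, and the protocol gives no basis for sizing it.

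The conclusion assumes that emergence starts at about the end of surgery, that transfer is brief, and that the opener may have a hand in the anaesthetic. If emergence starts 10 minutes or more after positioning, the interval disappears and only the undefined time point remains. Knowledge of the arm after positioning is a separate, disclosed limitation that this change would not remove.

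**What to change.** Reword section III.E so that the envelope is opened at transfer to the bed, immediately before the angle is set and after the readings during stitching have been taken. State who opens it, and record the opening time on the case report form. The wording should not prescribe when anaesthetic infusions stop, because the protocol does not give that sequence and the change does not need it.

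The protocol is written largely in the past tense. If conduct is complete, report the interval as a limitation in interpreting extubation time, and say that the blindness of the stitching readings cannot be assured.

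The cost is a short change to one section and one time field. The small downside is a few moments' less notice of the allocated angle at transfer. This is a cheap improvement.
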